### Objectives

The primary objective is to test the hypothesis that acupuncture, compared with conventional treatment, will lead to significant improvements in poststroke cognitive function as measured using standardized neuropsychological assessments. A secondary hypothesis is that acupuncture will modulate the functional connectivity within the DMN as detected by resting-state fMRI and that changes in DMN connectivity will correlate with improvements in cognitive performance.

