#### fMRI Scanning Scheme

A Siemens MAGNETOM Trio 3.0T magnetic resonance imager will be used for routine MRI scanning, resting-state fMRI, and diffusion tensor imaging (DTI) data collection. Both pre- and posttreatment scans will be conducted using this state-of-the-art imaging technology. For imaging data, false discovery rate correction will be used.

Conventional MRI scan sequence and parameters are as follows: (1) repetition time (TR)=600 ms, echo time (TE)=10 ms, layer thickness=5 mm, field of view (FOV)=240 mm, and matrix size=256 × 256 (T1-weighted image parameters); (2) TR=3000 ms, TE=113 ms, layer thickness=5 mm, FOV=240 mm, and matrix size=256 × 256 (T2-weighted image parameters); and (3) TR=8800 ms, TE=79 ms, layer thickness=5 mm, FOV=240 mm, and matrix size=256 × 256 (T2-weighted fluid-attenuated inversion recovery parameters).

The scanning sequence and parameters for fMRI are as follows. First, the anatomical data are collected via a T1-weighted 3D spoiled gradient–recalled sequence, and the volume images are obtained. The scanning parameters are TR=1900 ms, TE=2.26 ms, layer thickness=1 mm, FOV=250 mm, and matrix size=256 × 256. Second, the resting fMRI data are collected via real-time imaging processing. Gradient-recalled echo-planar imaging recalls the image with the following parameters: TR=2000 ms, TE=30 ms, continuous scanning of 30 layers, layer thickness=4 mm, FOV=200 mm, matrix size=64 × 64, and scanning time of approximately 8 minutes and 6 seconds.

The scanning sequence and parameters for DTI are as follows. First, the anatomical data are collected via a T1-weighted 3D spoiled gradient–recalled sequence, and the volume images are obtained. The scanning parameters are TR=1900 ms, TE=2.26 ms, layer thickness=1 mm, FOV=250 mm, and matrix size=256 × 256. Second, the DTI data are scanned through an echo-planar imaging sequence in the horizontal axis. The following parameters**―**TR=7200 ms, TE=104 ms, 49 layers, 2.5-mm thickness, number of excitations once, matrix size=128 × 128, FOV=240 × 240 mm, and 64 nonlinear diffusion gradients (b=0.1000 seconds per mm^2^)**―**are applied. The scanning duration is approximately 8 minutes and 11 seconds.

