### fMRI Statistical Analysis

After preprocessing, statistical analyses will be conducted with *P*<.05 as the significance threshold applying false discovery rate correction for multiple comparisons. The analysis will include the following:

DMN extraction: random 2-sample *t* tests will compare extracted DMN data between groups, with *P*<.05 considered statistically significant.Functional connectivity of the DMN: the posterior cingulate cortex, medial prefrontal cortex, and medial temporal lobe were defined as regions of interest (ROIs). Resting-state functional connections between ROIs will be calculated, and the time correlation coefficient will be obtained for the 2–independent sample *t* test.Structural connectivity of the DMN: fiber bundles between ROIs will be extracted from DTI data. The average fiber bundle length (mL), average diffusion rate (MD), and mean fractional anisotropy (mFA) will be calculated for each group and compared using 2-sample *t* tests.Correlation analysis: using correlation tests, MoCA, MMSE, MBI, and Medical Outcomes Study 36-Item Short-Form Health Survey scores; *r* values; and mL, mFA, and MD values will undergo statistical analysis. The Pearson correlation coefficient (*r*) will be obtained for the *t* test.

Multiple linear regression models will be used to examine associations between groups (acupuncture vs sham acupuncture) and posttreatment cognitive outcomes (MoCA and MMSE), adjusting for baseline covariates. Logistic regression will analyze dichotomized outcomes, and interaction terms will test moderating effects of demographic and clinical variables.

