**Brand New Insights**

A suite of analyses, including independent component analysis, functional connectivity analysis, and DTI analysis, will be conducted before and after the intervention to assess changes in activation patterns, functional connectivity, and structural connectivity within brain regions associated with the DMN. Correlation analyses between changes in DMN and cognitive function will be conducted to elucidate the neuroimaging correlates of the structural and functional changes within the DMN.

Crucially, all participants will receive standardized cognitive rehabilitation as part of routine clinical treatment throughout the trial, with both the acupuncture treatment group and the sham acupuncture group undergoing the same treatment regimen. This design intentionally sets cognitive training as a constant therapeutic background to isolate the specific effects of acupuncture from nonspecific placebo responses. Therefore, the observed differences between groups will solely represent the contribution of acupuncture points to neuropsychology rather than absolute treatment outcomes. This method rigorously controls cognitive training variables, precisely quantifies the incremental benefits of acupuncture based on evidence-based rehabilitation, and simulates real-world practice to demonstrate the clinical relevance of acupuncture as an adjunctive treatment. Consequently, effect sizes should be interpreted as the added value of acupuncture to a standard cognitive program, with the differences controlled via sham stimulation directly attributable to the specific neural stimulation mechanisms of acupoints.

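### The imaging analysis section names neither change nor the baseline scan, so it does not match the change-with-change hypothesis and gives up precision in the group comparisons

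*Protocol article*

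**What the plan says.** All places are in the Protocol article.

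- **Objectives.** The secondary hypothesis has two parts. The first is that "acupuncture will modulate the functional connectivity within the DMN as detected by resting-state fMRI". The second is that "changes in DMN connectivity will correlate with improvements in cognitive performance".
- **fMRI Scanning Scheme.** "Both pre- and posttreatment scans will be conducted using this state-of-the-art imaging technology". Table 1 ticks resting-state fMRI and DTI at baseline, week 4 and week 8. Data Management places primary and secondary outcome measurement at baseline and at the end of the 8 weeks.
- **fMRI Statistical Analysis, group comparisons.** Two-sample "tests will compare extracted DMN data between groups". For connectivity between regions of interest, "and the time correlation coefficient will be obtained for the" two-sample t test. Fibre length (mL), diffusion rate (MD) and fractional anisotropy (mFA) from DTI are compared in the same way. None of the three comparisons names a time point, a change value or the baseline scan.
- **fMRI Statistical Analysis, correlations.** The clinical side is described as "using correlation tests, MoCA, MMSE, MBI, and Medical Outcomes Study 36-Item Short-Form Health Survey scores". The imaging side is the r, mL, mFA and MD values. Change is not mentioned. The baseline-adjusted regression later in the section covers MoCA and MMSE only.
- **Discussion, Brand New Insights.** Imaging analyses are to be done before and after the intervention to look at change, and "Correlation analyses between changes in DMN and cognitive function will be conducted".

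**The concern.** The section that should fix the imaging analysis can be read as correlating levels with levels and comparing levels between groups. The hypothesis, and the Discussion, speak of change. A correlation between post-treatment levels answers a different question. After stroke, patients with poorer networks may also score worse on cognition whether or not treatment alters either. Such a correlation would not support the mechanistic reading that the Discussion hopes for, with its talk of treatment targets and imaging markers.

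The mismatch also leaves two different correlation analyses open once the data are in: the one in the Methods and the one in the Discussion. For the group comparisons the stake is smaller. The baseline scan is paid for and collected, but the stated tests do not use it, in a trial of only 54 participants.

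**Working it through.** The plan gives no figure on this point, so there is none to reproduce. The check is a comparison of the sections, followed by illustrations whose correlation inputs are assumed, because the document does not give them.

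**1. Sections side by side**

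| Place | Quantity related or compared |
|---|---|
| Objectives | change in DMN connectivity with improvement in cognition |
| fMRI Statistical Analysis | scores with r, mL, mFA, MD; groups on these values |
| Brand New Insights | changes in DMN with cognitive function |

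Only the middle row, the one in the Methods, omits change. The authors do name time or baseline for clinical outcomes: pre- and post-treatment differences under General Data and Efficacy Indicator Statistical Analysis, and baseline covariates for MoCA and MMSE.

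**2. Group comparison**

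Let ρ be the correlation between the baseline scan and the week-8 scan (assumed). The variance of the group contrast, relative to a t test on post-treatment values, is 2(1 − ρ) for a t test on change and 1 − ρ² for a linear model with the baseline value.

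| ρ | post only | change | baseline-adjusted |
|---|---|---|---|
| 0.3 | 1 | 1.40 | 0.91 |
| 0.5 | 1 | 1.00 | 0.75 |
| 0.7 | 1 | 0.60 | 0.51 |
| 0.8 | 1 | 0.40 | 0.36 |

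Adjustment removes 9% to 64% of the variance. A t test on change is worse than post-treatment values alone when ρ is below 0.5, so reading the stated t tests as tests of change does not secure the gain.

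**3. Correlation of levels against correlation of changes**

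Assume two measures with baseline SD 1 and baseline correlation a, and changes that are independent of baseline with SD 0.6 and correlation c. The post-treatment correlation is (a + 0.36c)/1.36. With 44 participants (the evaluable number in Sample Size), the chance of nominal significance is about Φ(atanh(r) × √41 − 1.96), plus a negligible lower tail.

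- Changes unrelated, a = 0.5, c = 0: r = 0.5/1.36 = 0.37. Then atanh(0.368) × 6.40 = 2.47, and Φ(0.51) is about 0.70. A simulation of this case gave 0.7045.
- Changes related, a = 0, c = 0.5: r = 0.18/1.36 = 0.13. Then atanh(0.132) × 6.40 = 0.85, so about 0.14 including the lower tail. The correlation of changes themselves (0.5) would be detected with Φ(0.549 × 6.40 − 1.96) = Φ(1.56), about 0.94.

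A second assumed model has a stable component carrying a share s of each measure's variance, stable components correlated k, and the rest uncorrelated. Then r = s × k.

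- s = 0.6, k = 0.5: r = 0.30, atanh(0.30) × 6.40 = 1.98, chance about 0.51.
- s = 0.3, k = 0.2: r = 0.06, chance about 0.07.
- s = 0.8, k = 0.5: r = 0.40, chance about 0.77.

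The direction is general, but the size follows the inputs. All these chances are at nominal 0.05; the section applies false discovery rate correction, which would lower them.

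**4. What a correlation of changes can detect**

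At two-sided 0.05 and 80% power, |r| = tanh((1.96 + 0.84)/√(n − 3)). For n = 44 this is tanh(0.4375) = 0.41; for n = 54, tanh(0.392) = 0.37.

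**5. Fisher z**

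A simulation with 22 per arm (assumed z-scale SD 0.3, difference 0.25) gave power of 0.763, 0.748 and 0.738 on raw coefficients and 0.770, 0.768 and 0.769 on Fisher z, at mean z of 0.3, 0.6 and 0.9. The gain is 0.7 to 3.1 points.

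**The case against.** The strongest reply is that the Discussion already commits to the right analysis, since it promises before-and-after imaging analyses and correlations of changes. The Methods list variables and tests without saying that they are post-treatment levels. A score can be a change score, and a two-sample t test can be run on changes. A condensed article may leave the derived variable to an analysis plan. This stands in part. A reader might infer that the mechanistic hypothesis is not tested at all, and the document does not support that. It does not remove the mismatch, because the section that specifies the tests is the one that omits change.

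A second reply is that omitting the baseline scan is no error. That stands too: in randomised groups, a t test on post-treatment imaging is unbiased for the treatment effect. A reader might infer that the group comparisons are invalid; they are not. The loss is precision only, and its size rests on an assumed ρ.

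Third, the chance of a misleading level correlation is not a property of this plan. It is the power to detect a real correlation of levels, and becomes an error only if that result is presented as a link between changes. The range of 7% to 77% shows how far it depends on inputs. This stands, so no single figure should be quoted as the error rate.

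Fourth, the scan wording may be shorthand. The sections on daily living and quality of life also speak of before and after treatment, while Table 1 ticks those scales three times, and week 8 is the natural reading of post-treatment. That is reasonable, but the section with the t tests still names no scan. Fisher z is, as the figures show, a minor refinement, and the section does not rule it out.

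**Conclusion.** The point holds as a mismatch and a missed gain in precision. The imaging section of the Methods does not specify the correlation of changes that the Objectives hypothesise and the Discussion promises, and its group comparisons do not use the baseline scan.

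For the group comparisons, the gain from adjustment is a variance factor of 0.91 to 0.36 for an assumed ρ of 0.3 to 0.8. For the correlation, levels can mislead in either direction, to an extent that cannot be fixed from the document. The hypothesis is secondary, the stated t tests are valid, and the primary MoCA analysis is not touched. The change should be made because it is cheap and removes a choice between two analyses.

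**What to change.** In fMRI Statistical Analysis:

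1. Compare groups on week-8 DMN connectivity, and on mFA, MD and mL, with a linear model containing group and the baseline value of the same metric. Fisher z for connectivity is a minor refinement.
2. State that the test of the second part of the secondary hypothesis is the correlation of change in DMN connectivity with change in MoCA, adjusted for group, so that a shift of both means by treatment cannot by itself produce it. Report it as associative.
3. Name week 8 as the comparison scan, and reconcile Table 1 (weeks 0, 4 and 8) with the pre- and post-treatment wording in fMRI Scanning Scheme and with Data Management.

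The cost is wording; the scans are already planned. Change scores are noisier than levels, so estimated correlations may be smaller, and 44 participants give 80% power only for |r| of about 0.41. Trial Status says the trial has not started and Results says that nobody is enrolled, so the change can be made before any data exist. Ethical Considerations requires committee approval for changes to analysis plans.

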### Ethical Considerations

This informed consent agreement is executed in adherence to the Declaration of Helsinki. The study protocol and consent form have received approval from the ethics committee of the First Affiliated Hospital of Nanchang University (approval 2020 12-86). All participants will receive comprehensive information about the trial and provide their informed consent through a signed agreement before taking part. All personal information will be kept confidential ― identifiable data will be stored separately from study data, replaced by coded IDs, and accessible only to the research team. Electronic records will be stored on encrypted, password-protected servers and paper forms in locked cabinets. No identifiable information will be reported in publications.

Any significant modifications to the protocol, such as changes to eligibility criteria, outcomes, or analysis plans, will be submitted to the research ethics committee for review and approval before implementation. The approved amendments will also be communicated promptly to all relevant parties, including the trial investigators, trial participants, trial registries, and relevant journals or regulatory bodies. These modifications will also be documented in an amendment log and will be audited at least annually to ensure consistency across the registered protocol and study documents.

### Trial Status

This protocol is version 1, dated August 20, 2025. The trial has not yet started.

## Results

We are currently in the recruitment phase, and we will publish the results in open-source journals when the trial is completed. As of August 2025, we have completed protocol finalization and ethics approval. Recruitment has begun, and no participants have been enrolled yet.

## Discussion

### Therapeutic Approaches

Currently, cognitive training stands as the predominant rehabilitation therapy for PSCI, demonstrating positive effects across various cognitive domains. Nevertheless, its efficacy is constrained by high demands on patients’ cognitive function, limiting its application in cases of severe cognitive dysfunction. Alternative therapies, including TCM, exercise, and music therapy, exhibit some potential in improving the cognitive function of patients with PSCI, yet their effectiveness remains unclear. Acupuncture, rooted in TCM principles, has been recognized by scholars for its positive impact on alleviating cognitive dysfunction in patients with PSCI. Notably, studies suggest that specific acupuncture points such as Baihui, Shenting, and Sishencong significantly enhance cognitive function in patients with PSCI [45,46]. However, the precise mechanisms through which acupuncture modulates brain function in patients with PSCI, particularly in the DMN brain region associated with cognitive function, remain unexplored.

In this trial, we have implemented a stringent randomized controlled study design, wherein patients diagnosed with PSCI are randomly allocated to either a sham acupuncture group or an acupuncture treatment group. Although cognitive function assessments typically involve subjective scales, we are enhancing the consistency and reliability of these assessments by providing standardized training for the evaluators and ensuring that each patient is assessed by the same evaluator. Furthermore, fMRI will be used to explore the neuroimaging mechanisms that underpin the effects of acupuncture, with the goal of offering valuable insights for clinical practice.

**Brand New Insights**

A suite of analyses, including independent component analysis, functional connectivity analysis, and DTI analysis, will be conducted before and after the intervention to assess changes in activation patterns, functional connectivity, and structural connectivity within brain regions associated with the DMN. Correlation analyses between changes in DMN and cognitive function will be conducted to elucidate the neuroimaging correlates of the structural and functional changes within the DMN.

Crucially, all participants will receive standardized cognitive rehabilitation as part of routine clinical treatment throughout the trial, with both the acupuncture treatment group and the sham acupuncture group undergoing the same treatment regimen. This design intentionally sets cognitive training as a constant therapeutic background to isolate the specific effects of acupuncture from nonspecific placebo responses. Therefore, the observed differences between groups will solely represent the contribution of acupuncture points to neuropsychology rather than absolute treatment outcomes. This method rigorously controls cognitive training variables, precisely quantifies the incremental benefits of acupuncture based on evidence-based rehabilitation, and simulates real-world practice to demonstrate the clinical relevance of acupuncture as an adjunctive treatment. Consequently, effect sizes should be interpreted as the added value of acupuncture to a standard cognitive program, with the differences controlled via sham stimulation directly attributable to the specific neural stimulation mechanisms of acupoints.

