### Randomization and Allocation Concealment

An impartial statistician will generate a concealed random allocation sequence using the PLAN procedure in the SAS statistical software (version 9.1; SAS Institute). Eligible participants will be randomly assigned in a 1:1 ratio to either the acupuncture treatment group or the conventional treatment control group. The random sequence will be securely stored and managed by a project manager who is not involved in participant recruitment, screening, or outcome assessment. To ensure allocation concealment, the group assignments will not be disclosed to screeners, evaluators, or participants during the enrollment process. Once a participant is deemed eligible and enrolled, the project manager will inform them of their group assignment via telephone, thus maintaining strict separation between the randomization process and other trial operations.

Given the nature of acupuncture, it is not feasible to blind the practitioners delivering the intervention. We acknowledge that the lack of practitioner blinding could introduce performance bias and influence internal validity through potential nonspecific or placebo effects. To minimize these risks, we will (1) blind participants to the specific study hypotheses and expected effects of each intervention, (2) ensure that outcome assessors and statisticians remain blinded throughout the trial, (3) standardize the practitioner-patient interaction by using scripted instructions and limiting nonprotocol communication, and (4) provide the control group with conventional treatment to control for attention and treatment expectancy effects. These measures aim to reduce expectancy bias and placebo responses, thereby strengthening the internal validity of the trial despite the inherent limitations of acupuncture blinding.

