### Blinding

This study will use a single-blind design in which both the participants and the primary outcome assessors will remain blinded to group assignments. A designated project manager will oversee the generation of the randomization sequence and the allocation of blinding codes. Group assignments will be generated using a computer-based random number table and anonymized as group A or B.

Given the inherently distinguishable nature of acupuncture interventions, blinding of treating physicians is not feasible. However, all treating physicians will undergo standardized training to ensure consistent procedures and neutral communication, thereby minimizing observer bias.

Participants will be randomly assigned to either the acupuncture group or the conventional treatment group. To maintain participant-level blinding, the conventional treatment group will receive sham acupuncture using specially designed nonpenetrating needles applied to nonacupoint locations. The procedures, including manipulation, duration, and frequency, will be identical in both groups to ensure comparable treatment experiences.

Outcome assessors and statistical analysts will be blinded to the actual group identities and will only have access to anonymized labels (A or B). Conversely, treating physicians and project managers will not participate in outcome assessment or data analysis. Similarly, outcome assessors and analysts will not be involved in participant enrollment or allocation.

The blinding code will be securely sealed and will not be disclosed until the completion of all statistical analyses.

To assess the success of blinding, participants will be asked at the end of the treatment period to indicate which group they believe they were assigned to (A, B, or unsure) via a structured questionnaire.

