##### Sham Acupuncture Procedure

Sham acupuncture will be administered at nonacupoint sites approximately 2 cm posterior to Baihui (GV20), 1.5 cm lateral to Shenting (GV24), and 2 cm adjacent to Sishencong (EX-HN1), avoiding recognized meridians [40]. A nonpenetrating placebo needle will provide superficial tactile pressure without skin penetration, mimicking real acupuncture sensation but avoiding physiological effects [41]. Sessions will last 20 minutes once daily, 5 days per week for 8 weeks.

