#### Acupuncture Treatment Group

##### Overview

Participants will receive all the aforementioned conventional therapy components and real acupuncture in place of sham acupuncture. Selected acupoints will include GV20, GV24, and EX-HN1. Disposable sterile filiform needles will be inserted to a depth of 10 to 15 mm and manipulated to elicit *deqi* sensation. Each session will last 20 minutes once daily, 5 days per week for 8 weeks.

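### The planned reading of the group difference as an effect of acupuncture points alone is not identified: site, skin penetration and deqi manipulation differ together between the two arms

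*Protocol article*

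**What the plan says.** **Interpretation.** Brand New Insights, in the Discussion, says that "the observed differences between groups will solely represent the contribution of acupuncture points to neuropsychology" and that sham-controlled differences are "directly attributable to the specific neural stimulation mechanisms of acupoints". Between these two statements it gives a broader reading: "effect sizes should be interpreted as the added value of acupuncture to a standard cognitive program".

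**The arms.** For the control, Sham Acupuncture Procedure places needles at non-acupoint sites about 1.5 to 2 cm from the real points and states: "A nonpenetrating placebo needle will provide superficial tactile pressure without skin penetration". For the active arm, the Overview under Acupuncture Treatment Group has needles at the three named acupoints, "inserted to a depth of 10 to 15 mm and manipulated to elicit" deqi. The Blinding section nevertheless says: "The procedures, including manipulation, duration, and frequency, will be identical in both groups".

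**The comparator.** The primary objective is that "acupuncture, compared with conventional treatment, will lead to significant improvements in poststroke cognitive function". Study Design also calls the control a conventional treatment group. Randomization and Allocation Concealment lists, among its measures against bias, to "provide the control group with conventional treatment to control for attention and treatment expectancy effects". The Abstract, Table 1, fMRI Statistical Analysis and the opening section of the Discussion name sham acupuncture instead.

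**The concern.** A statement that a difference comes only from acupuncture points requires arms that differ only in the points. These arms also differ in whether the skin is pierced and, as described, in whether the needle is worked to produce deqi. If the trial is positive, the report would carry a point-specific mechanism that the data cannot separate from the effect of piercing and manipulating needles anywhere on the scalp. The same two arms supply the default mode network comparisons, so the attribution would pass into the imaging conclusions, which are a main aim of the study.

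The comparator label adds to this. The primary objective should say which contrast is tested. As worded, it leaves out the sham that the control group receives. The statement on expectancy likewise credits conventional treatment, which both arms receive. Only the sham can balance expectations about needling.

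**Working it through.** No figure in the protocol belongs to this point, so the check sets the sections side by side and counts what two arms can identify.

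**Step 1: compare the arms.**

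| Feature | Active arm (Overview) | Control arm (Sham Acupuncture Procedure) | Same? |
|---|---|---|---|
| Conventional therapy | yes | yes | yes |
| Session length and schedule | 20 min daily, 5 days a week, 8 weeks | 20 min daily, 5 days a week, 8 weeks | yes |
| Site | three acupoints | non-acupoints, about 1.5 to 2 cm away | no |
| Penetration | 10 to 15 mm | none | no |
| Manipulation for deqi | specified | not specified; superficial tactile pressure | no, as described |

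**Step 2: write out the contrast.** Let S, P and M be the effects of site, penetration and manipulation, I their interactions, and B any bias from unblinded practitioners. The expected difference between arms is

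D = S + P + M + I + B.

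The trial estimates D. Reading D as S requires P + M + I + B = 0, and the protocol neither argues nor can test this. Three components enter and one independent contrast is available (2 arms − 1 = 1). A given D is compatible with S equal to all of it, part of it or none of it.

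**Step 3: ask which comparison would isolate site.** It would need a group that differs from one of the two arms in site only: real needling at non-acupoints, or the non-penetrating needle at acupoints. Neither group exists, so no choice of model or covariates can recover S.

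**Step 4: check dependence on the manipulation question.** If manipulation were the same in both arms, as Blinding states, M would drop out, leaving D = S + P + I + B. Site and penetration still change together, so S is still not identified.

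**Step 5: check what the protocol's argument removes.** Brand New Insights reasons from cognitive training being constant across arms. That removes cognitive training as an explanation of D and leaves S, P, M, I and B untouched. On B, Randomization and Allocation Concealment itself concedes that unblinded practitioners may introduce performance bias and placebo effects, which does not sit with an exclusive attribution.

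**Step 6: look for a withdrawal of the claim.** Limitations and Future Directions discusses incomplete blinding, reduced contrast from shared training, and generalizability. It does not mention that site, penetration and manipulation are confounded.

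**The case against.** The strongest reply is that the trial is sound for its efficacy question and the fault is loose Discussion prose. Real versus non-penetrating sham needling on a shared background is a coherent contrast. The objectives contain no hypothesis of point specificity, the conclusions speak of acupuncture as a whole, and the disputed sentence goes on to distinguish incremental from absolute benefit. This stands as a limit on the consequence. It does not rescue the two attribution clauses: the second names acupoint mechanisms outright, and both tell the reader in advance how to interpret the result.

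Three stronger readings are tempting, and the documents do not support them.

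- *The primary objective tests acupuncture against no needling.* No section describes a no-needle control. Blinding says that the conventional treatment group receives sham, the sham procedure is listed under that group's heading, and the regression analysis is specified as acupuncture against sham. The objective carries an inconsistent label, not a second contrast.
- *Expectancy is uncontrolled.* Blinding ties the sham to participant blinding. The randomization section credits the wrong component, but the control exists.
- *Blinding claims that the arms are the same in every respect.* The sentence just before the claim discloses the non-penetrating needle and the non-acupoint sites. Only manipulation is in conflict, and even there the sham section does not say that the needle is left unmanipulated; deqi is simply specified for one arm only.

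**Conclusion.** The point holds as one of interpretation and labelling. Three needling components, or two if manipulation proves to be matched, are confounded in a single contrast, so the exclusive attribution to acupuncture points is not identified. What the trial can estimate is the effect of the real-needling package relative to the sham package, each added to the same conventional therapy. Any practitioner effect is included in that estimate.

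The comparator wording is a naming inconsistency. It deserves correction because it sits in the primary objective and in the expectancy statement. A null result should be reported as no demonstrated difference from sham. It would not show that needling adds nothing to conventional care, a question that this design does not address.

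The conclusion rests on the arm descriptions as printed and on there being two arms only. It does not call the sham control a wrong choice. Randomization, outcomes, tests and sample size are unaffected.

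**What to change.** 1. In Brand New Insights, replace both attribution clauses with: the combined effect of real needling (site, penetration and manipulation) relative to non-penetrating sham at non-acupoints, both added to conventional rehabilitation.
2. In Objectives, state the primary comparison as acupuncture versus sham acupuncture, both added to conventional treatment. Use that comparator name in Study Design, Randomization and Allocation Concealment, and Blinding.
3. In Randomization and Allocation Concealment, name the sham procedure as the control for needling expectancy.
4. Reconcile the Blinding statement on manipulation with Sham Acupuncture Procedure and the active-arm Overview, so that all three describe the same thing. How the needles are to be manipulated is for the investigators to settle.

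The cost is wording and a narrower conclusion. The Results section reports no participant enrolled as of August 2025, so the changes can precede any data. If rewording the objective counts as a significant modification, it goes through the ethics review that the protocol already provides for. A claim about point location itself would need a different design; this correction does not require one.
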